# Protocol for the mWellcare trial: a multicentre, cluster randomised, 12-month, controlled trial to compare the effectiveness of mWellcare, an mHealth system for an integrated management of patients with hypertension and diabetes, versus enhanced usual care in India

**DOI:** 10.1136/bmjopen-2016-014851

**Published:** 2017-08-11

**Keywords:** hypertension, diabetes, mHealth, decision support system, integrated management of chronic conditions

## Abstract

**Introduction:**

Rising burden of cardiovascular disease (CVD) and diabetes is a major challenge to the health system in India. Innovative approaches such as mobile phone technology (mHealth) for electronic decision support in delivering evidence-based and integrated care for hypertension, diabetes and comorbid depression have potential to transform the primary healthcare system.

**Methods and analysis:**

mWellcare trial is a multicentre, cluster randomised controlled trial evaluating the clinical and cost-effectiveness of a mHealth system and nurse managed care for people with hypertension and diabetes in rural India. mWellcare system is an Android-based mobile application designed to generate algorithm-based clinical management prompts for treating hypertension and diabetes and also capable of storing health records, sending alerts and reminders for follow-up and adherence to medication. We recruited a total of 3702 participants from 40 Community Health Centres (CHCs), with ≥90 at each of the CHCs in the intervention and control (enhanced care) arms. The primary outcome is the difference in mean change (from baseline to 1 year) in systolic blood pressure and glycated haemoglobin (HbA1c) between the two treatment arms. The secondary outcomes are difference in mean change from baseline to 1 year in fasting plasma glucose, total cholesterol, predicted 10-year risk of CVD, depression, smoking behaviour, body mass index and alcohol use between the two treatment arms and cost-effectiveness.

**Ethics and dissemination:**

The study has been approved by the institutional Ethics Committees at Public Health Foundation of India and the London School of Hygiene and Tropical Medicine. Findings will be disseminated widely through peer-reviewed publications, conference presentations and other mechanisms.

**Trial registration:**

mWellcare trial is registered with Clinicaltrial.gov (Registration number NCT02480062; Pre-results) and Clinical Trial Registry of India (Registration number CTRI/2016/02/006641). The current version of the protocol is Version 2 dated 19 October 2015 and the study sponsor is Public Health Foundation of India, Gurgaon, India (www.phfi.org).

Strengths and limitations of the studymWellcare trial is the first study in India, assessing the effectiveness of mHealth technology for integrated management of hypertension and diabetes at primary care level in a public health setting.The study follows a cluster randomised controlled trial design.The study uses nurse for shifting/sharing some of the patient management tasks from physicians.The Intervention provides clinical decision support to physician for standardised and integrated management of hypertension and diabetes along with comorbid conditions such as depression and alcohol use disorder.The mWellcare intervention is being implemented in the real-world scenario aimed at using the existing human resource with an aim of scalability.Effectiveness of the trial will also depend on the availability of drugs recommended by the decision support system. Drugs are supplied by the state government and there are variations in availability across the state and districts, although such variations are likely to affect both arms equally.

## Background and rationale

Cardiovascular disease (CVD) and diabetes are the leading causes of premature (<60 years) adult deaths in India with projections indicating almost threefold increase to 18 million premature years of life lost by 2030, a greater loss of life than the combined projected burdens for China, Russia and the USA.^1 2^ CVD and diabetes will result in $2.32 trillion loss in national income in India between 2012 and 2030.^3^ Primary care is considered as the appropriate setting for the prevention and control of chronic conditions and it is being strengthened through the National Programme for Prevention and Control of cancer, diabetes, cardiovascular diseases and stroke (NPCDCS) in India.^2 4 5^

The telecom industry in India has grown exponentially over past 15 years, from under 3.6 million mobile phone subscribers in March 2001 to over a billion subscribers in December 2015.^6^ Mobile phones and other mobile technologies require less infrastructure than other eHealth systems, making them a promising investment for developing countries wanting to strengthen and transform their weak health systems, and to overcome healthcare worker shortages.^7–9^ Systematic reviews have demonstrated a lack of robust evaluations of the impact of mHealth.^10–14^ This lack of adequate evaluations led to need to provide robust evidence on the safety, benefits and associated cost-effectiveness of mHealth systems.^8 9 15 16^ Systematic review and meta-analysis of studies evaluating role of decision support system for prevention of CVD show paucity of well-designed studies on patient outcomes.^17^ In addition, there is a dearth of evidence on effect of task shifting/sharing strategies for CVD risk reduction and chronic disease management.^18 19^ Through mWellcare we propose to enhance the quality of hypertension and diabetes care at primary care level in India by using mobile phone technology that implements a clinical decision support system and electronic health records for the use of healthcare professionals. The effectiveness of the mHealth system will be tested on a range of clinical and process-of-care indicators.

## Methods and analysis

### Objective

The primary objective is to evaluate mWellcare system in two states in India over a 12-month period to determine its effectiveness on the management of patients with hypertension and/or diabetes based on their clinical outcomes (systolic blood pressure (SBP) and HbA1c) compared with an enhanced care arm using a cluster randomised study design.

Secondary objective is to assess the impact of the mWellcare system on change in cardiovascular risk factors (body mass index (BMI), alcohol use, tobacco use) and 10-year CVD risk score, mental health status, process outcomes and cost-effectiveness.

### Trial design

mWellcare is a cluster randomised controlled trial with equal allocation of participants between intervention and enhanced care arms.

### Study setting

Twenty clusters each from two states: one in the north and the other in the south India have been selected for the trial. Each cluster is a Community Health Centre (CHC) which caters to a rural population of 120 000 and serves as a referral centre for four Primary Health Centres (PHCs) in the formal healthcare delivery system.^20^ CHCs were selected from districts covered under the NPCDCS. Allocation of the CHCs into intervention and control arm is described in the section on randomisation.

### Inclusion criteria

Participants aged 30 years and above intending to reside in the catchment area of CHCs for at least next 12 months were eligible for the trial. Participants were included if they were diagnosed case of hypertension with blood pressure measuring ≥140/90 mm Hg or type 2 diabetes mellitus with fasting blood sugar ≥140 mg/dL or postprandial blood sugar ≥200 mg/dL and if they provided informed consent.

### Exclusion criteria

Pregnant women, patients with type 1 diabetes, patients requiring immediate referral to tertiary care due to accelerated hypertension or diabetic complications, patients with learning difficulties or vision and/or hearing impairments, patient suffering from malignancy or life-threatening disease with death probable in 4 years and patients not residing in the catchment area of the CHC were excluded.

### Intervention

In the intervention arm, nurse and physician are providing treatment and follow‐up to recruited participants using mWellcare system. mWellcare system is a tablet computer-based Android application that is designed to store the health records electronically, provides decision support recommendation tailored to the participant’s compliance and risk level, enables long-term monitoring and follow-up and sends SMS reminders (to take medication and follow-up visits) to patient. Development of intervention involved adapting existing clinical management guidelines to the local context, development and validation of clinical algorithm and pilot testing of mWellcare system. Nurses and physicians in the intervention arm were trained in the use of mWellcare system and also provided ‘refresher’ training on the clinical management guidelines for hypertension and diabetes.

In the intervention arm, besides baseline information, the nurse enters information on comorbid conditions: depression (using patient health questionnaire 9), alcohol use disorder (using alcohol use disorder identification test) and previous medication details into mWellcare system and generates and prints decision support recommendation (DSR) for the physician. The DSR printout consists of patient profile, diagnosed condition, comorbid conditions, previous and current medication and recommended treatment plan. It also provides lifestyle change recommendation and the date of the next follow-up visit. After review of the DSR, the physician may agree or suggest changes in the treatment plan which is recorded in the application. Nurse provides lifestyle advice brochure (in local language) and explains the same to each participant. Each participant will be followed up for 12 months. During this period, participants will receive SMS reminders for follow-up visits scheduled as per clinical algorithm. During follow-up visits, nurse enters relevant parameter to the patient’s clinical record and generates DSR printout for physician’s review. Each intervention site gets monthly reports on number of participants reporting for scheduled follow-up and average change in clinical parameters.

In the enhanced care arm, nurse and physicians were provided ‘refresher’ training on the clinical management guidelines for hypertension and diabetes. In addition, charts on management of these conditions were provided to the facilities for prominent display at the outpatient department. Physicians in the enhanced care arm provide the management plan based on their assessment of clinical parameters of the participants. Nurse provides lifestyle advice brochure (in local language) and explains the same to each participant. Follow-up in the enhanced care arm is based on the assessment of clinical parameters of the participants by the physician.

### Outcomes

#### Primary outcomes

Difference in mean change (from baseline to 1 year) in SBP between the two treatment arms.Difference in mean change (from baseline to 1 year) glycated haemoglobin (HbA1c) between the two treatment arms.

#### Secondary outcomes include

Difference in mean change (from baseline to 1 year) between the two treatment arms for fasting plasma glucose, total cholesterol and predicted 10-year risk of CVD using recalibrated Framingham risk score.Differences in risk factors such as depression/anxiety, smoking behaviour, BMI and alcohol use between the two treatment arms.Comparison of costs associated with delivering the mWellcare intervention arm with respect to enhanced care.

### Participant timeline

Enrolment and baseline assessment were done during the first visit, and the participants were asked to come back for blood sample collection (for HbA1C and total cholesterol tests) within 2 weeks. The intervention started on the first visit and will continue for 12 months. After 12 months, endline assessment will be done.

### Sample size calculation

The primary outcomes will be analysed as the average change of the biomarker (SBP) and glycated haemoglobin (HbA1c)) from baseline to 12-month follow-up in each participant. In each of the trial arms, there will be an average change and the effect of the intervention will be the difference of these averages.

A recruitment of 40 participants with hypertension per cluster in 40 clusters will yield over 98% power with a type I error of 5% to detect a mean difference of the change of 4 mm Hg in SBP, between the intervention and enhanced care arm assuming a 15 mm Hg SD of the changes in both arms and an intraclass correlation (ICC)=0.05.^21^ A number of 40 participants with diabetes per cluster will yield a power above 99% for detecting a true difference in average change of HbA1c between the two arms of 0.37%, assuming a 1.1% SD of the changes in both arms and an ICC=0.04.^22 23^

All calculations are based on the formula for comparison of two means in cluster randomised trials proposed by Hayes and Bennett and assume a 20% loss to follow-up.^24^

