### Recruitment

For the two primary outcomes (SBP and HbA1c), we planned to recruit a total of 90 participants per site with a minimum of 45 participants with each conditions: hypertension and diabetes. We estimated that the recruitment could be completed in 2 months enrolling a minimum of two to three participants a day. However, some sites had lower recruitment rate for either of the two conditions. Therefore, the final strategy was to stop recruitment of participants with either condition after reaching 45, and then complete recruitment of patient with the other condition. A total of 3702 participants were recruited from 40 CHCs.

All individuals diagnosed to have hypertension and/or type 2 diabetes were assessed for eligibility by the nurse. All eligible participants were invited to participate in the trial. After providing written and verbal information about the trial, written consent was obtained by the nurse. The flow of trial participant is depicted in figure 1.

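### The stated SBP power of over 98% does not follow from 20 CHCs per arm; the plan's own inputs give about 83 to 85%

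*Protocol article*

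**What the plan says.** The protocol article, under Sample size calculation, gives one power statement for each primary outcome. For SBP: "A recruitment of 40 participants with hypertension per cluster in 40 clusters will yield over 98% power with a type I error of 5" per cent. The target is a 4 mm Hg difference in mean change, with an SD of change of 15 mm Hg and an ICC of 0.05. For HbA1c: "A number of 40 participants with diabetes per cluster will yield a power above 99" per cent, for a difference of 0.37 percentage points, SD 1.1 and ICC 0.04. The section says that all calculations use the Hayes and Bennett formula for two means and "assume a 20% loss to follow-up".

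Other sections fix the number of clusters. Study setting says "Twenty clusters each from two states: one in the north and the other in the south India have been selected for the trial", which makes 40 CHCs in all. Recruitment agrees: "A total of 3702 participants were recruited from 40 CHCs". Trial design specifies equal allocation, and Randomisation uses blocks of two within strata of 20, 10 and 10 CHCs. Each arm therefore has 20 CHCs.

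**The concern.** In a cluster trial, the number of clusters per arm limits power. With 20 per arm and an ICC of 0.05, over 98% power for a difference of about a quarter of an SD (4/15 = 0.27) looks too high.

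SBP is one of two primary outcomes. A reader told that power exceeds 98% will take a non-significant SBP result as near-proof that a 4 mm Hg benefit is absent. The section on economic evaluation adds to this: if the primary outcomes show no significant difference, it moves to a cost-minimisation analysis, which treats the arms as equally effective. The stated power makes that step look safer than the design supports.

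**Working it through.** **Inputs**

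- Clusters per arm: c = 40/2 = 20 (Study setting, Trial design, Randomisation).
- Analysed per CHC and condition: m = 40 × 0.8 = 32 (Sample size calculation).
- SBP: δ = 4 mm Hg, SD = 15 mm Hg, ICC = 0.05.
- HbA1c: δ = 0.37, SD = 1.1, ICC = 0.04.
- Type I error 5%. The section does not say whether one- or two-sided; two-sided is taken here and one-sided is tried below.

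**Formulas**

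- Design effect: DE = 1 + (m − 1) × ICC
- SE = SD × √[2 × DE / (c × m)]
- Power = Φ(δ/SE − 1.96)
- The Hayes-Bennett formula adds one cluster per arm to the requirement, so for a fixed design c is replaced by c − 1 = 19.

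**Reproducing the stated figures.** They come out if 40 is entered as the number of CHCs per arm, with m = 32:

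- SBP: SE = 15 × √[2 × 2.55/(40 × 32)] = 0.947; power = Φ(4.22 − 1.96) = 98.8% (98.7% with c − 1 = 39).
- HbA1c: power is 99.99%.

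**SBP with 20 CHCs per arm**

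- DE = 1 + 31 × 0.05 = 2.55
- SE = 15 × √[2 × 2.55/(20 × 32)] = 1.339 mm Hg
- Power = Φ(4/1.339 − 1.96) = Φ(1.03) = 84.8%
- With c − 1 = 19: SE = 1.374 and power = 82.9%. A noncentral t calculation on 38 df also gives 82.9%.

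**HbA1c with 20 CHCs per arm**

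- DE = 1 + 31 × 0.04 = 2.24
- SE = 1.1 × √[2 × 2.24/(20 × 32)] = 0.0920
- Power = Φ(0.37/0.0920 − 1.96) = 98.0%; with c − 1, 97.5%.

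**Other readings, 20 CHCs per arm**

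| Reading | SBP power (with c − 1) | HbA1c power (with c − 1) |
|---|---|---|
| 32 analysed, two-sided | 84.8% (82.9%) | 98.0% (97.5%) |
| 36 analysed (45 recruited, 20% loss) | 86.2% (84.5%) | 98.5% (98.0%) |
| 40 analysed (no loss) | 87.4% (85.7%) | 98.8% (98.4%) |
| 45 analysed (45 recruited, no loss) | 88.5% (86.9%) | 99.0% (98.7%) |
| 32 analysed, one-sided 5% | 91.0% (89.7%) | 99.1% (98.9%) |
| 45 analysed, one-sided 5% | 93.5% (92.5%) | 99.6% (99.5%) |

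If the SD of 15 is read as a within-cluster SD, SBP power at 32 analysed is lower: 82.9%, or 81.0% with c − 1.

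**Ceiling for SBP.** As m grows without limit, SE tends to 15 × √(2 × 0.05/20) = 1.061 mm Hg. Two-sided power then tends to Φ(3.77 − 1.96) = 96.5%, so no cluster size reaches 98%. One-sided, the limit is 98.3%, or 97.9% with c − 1.

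**What 98% SBP power would need at 32 analysed** (changing one input at a time)

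- About 36 CHCs per arm (37 with the extra cluster), or
- an SD of change of 11.2 mm Hg, or
- an ICC of 0.013, or
- a true difference of (1.96 + 2.054) × 1.339 = 5.4 mm Hg.

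At 90% power the detectable difference is (1.96 + 1.282) × 1.339 = 4.3 mm Hg, or 3.242 × 1.374 = 4.5 mm Hg with c − 1.

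**The case against.** The SBP shortfall itself is hard to dispute, but the point should not be pressed too far.

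- **HbA1c.** The gap is only 1.0 to 1.5 points, and it closes under a one-sided 5% test (99.1%). This stands. HbA1c only corroborates the SBP error.
- **Cause.** The mix-up of total and per-arm clusters is inferred; the document does not state it. Dropping the design effect would also exceed both stated figures (99.8% for SBP, over 99.9% for HbA1c). That would contradict the ICCs given in the same sentences, so the mix-up is the likelier explanation, but it remains an inference.
- **Ceiling.** The statement that no cluster size reaches 98% holds for a two-sided test. One-sided without the extra cluster, the limit is just above 98%, but only with unlimited participants per CHC.
- **Actual power may differ.** Recruitment planned at least 45 per condition, and the mixed model adjusts for baseline, which may add precision. The first raises SBP power only to about 84 to 86%. The second is not an input to the stated calculation, which uses the SD of changes.
- **Consequence.** Corrected SBP power is still above 80%, recruitment is complete, and the cost-minimisation step depends on significance, not on the stated power. All true. The error affects how a null result will be read and does not make the design inadequate.

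**Conclusion.** The concern holds. On the plan's own inputs, with 20 CHCs per arm and 32 analysed per CHC, two-sided SBP power is about 83 to 85%, which is 13 to 15 points below the stated 98%. The risk of missing a true 4 mm Hg difference is 15 to 17%, roughly eight times the stated risk of under 2%. HbA1c power is 97.5 to 98.0% against the stated 99%, a minor discrepancy.

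The range assumes that 40 is the number recruited, as the section words it, and that the SD of 15 mm Hg is the total SD of change. If 40 were the number analysed, SBP power would be about 86 to 87%, and the conclusion would not change.

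**What to change.** Correct the paragraph under Sample size calculation, and any analysis plan or report that repeats its figures:

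1. State that the design has 20 CHCs per arm and 32 analysed per CHC and condition after 20% loss, and state the sidedness of the 5% test.
2. Give power as about 83 to 85% for 4 mm Hg in SBP and about 97 to 98% for 0.37 percentage points in HbA1c (two-sided).
3. Add the SBP difference detectable with 90% power: about 4.3 mm Hg, or 4.5 mm Hg with the Hayes-Bennett extra cluster.
4. Say that a non-significant SBP result will be interpreted through its confidence interval, including before any cost-minimisation analysis that treats the arms as equally effective.

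The cost is a wording correction and a less favourable power figure. Enrolment, conduct and the primary model do not change.

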### Recruitment

For the two primary outcomes (SBP and HbA1c), we planned to recruit a total of 90 participants per site with a minimum of 45 participants with each conditions: hypertension and diabetes. We estimated that the recruitment could be completed in 2 months enrolling a minimum of two to three participants a day. However, some sites had lower recruitment rate for either of the two conditions. Therefore, the final strategy was to stop recruitment of participants with either condition after reaching 45, and then complete recruitment of patient with the other condition. A total of 3702 participants were recruited from 40 CHCs.

All individuals diagnosed to have hypertension and/or type 2 diabetes were assessed for eligibility by the nurse. All eligible participants were invited to participate in the trial. After providing written and verbal information about the trial, written consent was obtained by the nurse. The flow of trial participant is depicted in figure 1.

**Figure 1 F1:**
[figure not shown]
Trial flowchart. AUDIT, Alcohol Use Disorder Identification Test; BP, blood pressure; CHC, community health centre; FPG, fasting plasma glucose; NCD, non-communicable disease; PHQ9, patient health questionnaire; PPG, post-prandial glucose; SMS, short message service.

### Randomisation

Randomisation units are clusters (CHCs). The randomisation list was generated by a statistician independent of the trial using STATA SE V. 12. The list was stratified by states (Haryana and Karnataka) and within states by availability/non-availability of nurses recruited under NPCDCS. In Karnataka, stratification based on availability of nurses was done allocating 10 clusters in each category (nurse available under NPCDCS/not available). In Haryana, as there was no nurses recruited under NPCDCS, further stratification was not done. Clusters (CHCs) within each strata were randomised to intervention or enhanced care arm using block randomisation (with a block size of 2). Being a cluster randomised trial, only limited blinding could be enforced. The study statistician will remain blinded throughout the study until database is locked and study unblinded.

### Data collection, management and analysis

#### Baseline assessment

After consent, the nurse in both arms collected baseline data for the following parameters using a tablet computer: age, gender, marital status, occupation, alcohol use, smoking behaviour, health-related quality of life measured using EuroQol five dimensions questionnaire (EQ-5D), height, weight, blood pressure and blood sugar. Consented participants were asked to return on a scheduled day for blood sample collection for HbA1c and total cholesterol.

